# Randomized control trial of ultrasound-guided erector spinae block versus shoulder periarticular anesthetic infiltration for pain control after arthroscopic shoulder surgery

**DOI:** 10.1097/MD.0000000000019721

**Published:** 2020-04-10

**Keywords:** arthroscopic shoulder surgery, erector spinae plane block, periarticular infiltration, postoperative pain

## Abstract

Supplemental Digital Content is available in the text

## Introduction

1

Arthroscopic shoulder surgical repairs are common procedures performed to address different shoulder pathologies. Despite the fact that it is minimally invasive, it is often associated with moderate to severe postoperative pain that may interfere with the patients’ well-being, recovery and rehabilitation, and potentially increases hospital length of stay.^[1]^ The use of opioids to manage immediate postoperative pain is frequently associated with nausea, vomiting, respiratory depression, hormonal effects, and dysphoria.^[2]^ As such, achieving pain control while minimizing opioid use is critical, since more than 60% of unplanned prolonged hospitalizations and hospital readmissions are thought to be related to inadequate pain control or to side effects of opioids.^[3]^

A number of techniques have been used to achieve good pain control after shoulder surgery, including periarticular infiltration (PAI) with local anesthetic (LA) and regional anesthetic blocks. Although shoulder PAI has been shown to decrease shoulder pain and opioid consumption,^4^,^5^,^6^ it is not as effective as regional blocks, such as the interscalene nerve block (ISNB).^7^,^8^ ISNB is considered the gold standard of regional nerve blocks for shoulder surgery but has the potential for significant side effects, such as persistent neurologic complications, rebound pain, phrenic nerve palsy, respiratory distress, cardiac arrest, pneumothorax, and central nerve toxicity.^9^,^10^,^11^,^12^,^13^ In view of this, investigating alternate regional blocks having the potential for good pain relief with minimal side effects is important.

The erector spinae plane (ESP) block can be considered as a modification of the thoracic paravertebral block, which blocks thoracic spinal nerves using injections outside of the conventional paravertebral space.^[14]^ It was first described by Forero et al in 2016 in case reports of 2 patients of severe thoracic neuropathic pain as well as 2 cases of acute postsurgical pain following video-assisted thoracoscopic wedge resection and lobectomy.^[15]^ The ESP block demonstrated a unilateral cutaneous sensory block of the posterior, lateral, and anterior chest wall as well as relief of neuropathic pain in these cases.^[15]^ ESP block is performed under ultrasound (US) by injecting LA deep to the erector spinae muscle at the interfascial space between either the erector spinae muscle and the rhomboid major muscle (higher up), or between the erector spinae muscle and the external intercostal muscles, at lower sites.^[15]^ Cadaveric studies of US-guided ESP blocks with methylene blue dye and subsequent dissection, as well an ESP block with a dye mixture and computed tomography scanning demonstrated that when injecting deep to the erector spinae the block likely affects the ventral and dorsal rami leading to the sensory blockade.^[15]^ The advantages include its simplicity and safety by limiting the risk of nerve damage and pneumothorax.^15^,^16^ Subsequent case reports have demonstrated ESP to be effective for abdominal surgery,^17^,^18^ breast and axillary surgery,^[19]^ and open radical cystoprostatectomy with ureter and bladder reconstruction.^[20]^ Recent case reports have explored its potential use for shoulder surgery when performed at a higher level (such as T2-T3). Forero et al reported successful management of chronic shoulder pain without motor blockade, with ESP performed at T3 level.^[21]^ A case report demonstrated ESP block used for shoulder surgery in 3 patients with variable success for postoperative analgesia.^[22]^

Our literature search of PubMed did not identify any randomized controlled trial (RCT) comparing ESP block to PAI or ISNB. We also looked to identify studies that have utilized ESP for post-surgical shoulder pain. There was only 1 case report of ESP for shoulder surgery.^[22]^ A search of clinicaltrial.gov revealed only 1 RCT examining ESP against ISNB for arthroscopic shoulder surgery, which is in the recruitment phase (https://clinicaltrials.gov/ct2/show/NCT03807505). Given the potential to provide effective sensory blockade with minimal technical risks, we think it is important to study the utility of ESP for arthroscopic shoulder surgeries. Currently, the ISNB is the preferred method for shoulder surgery analgesia, but it has associated risks of diaphragm paralysis and rebound pain.^23^,^24^ Given the importance of providing adequate analgesia for arthroscopic shoulder surgery and lack of consensus among surgeons and anesthesiologists for the optimal analgesic technique, we designed this RCT to compare the ESP blockade versus PAI of LA in patients undergoing arthroscopic shoulder surgery. Although it is important to establish the efficacy of ESP for shoulder surgery by comparing it with an inactive or placebo treatment, placebo injections can be considered unethical and may not be appealing to patients. On the other hand, comparing against an inactive treatment (such as no injection) can introduce potential bias and affects the internal validity of the study. Although PAI in the shoulder has been shown to decrease pain and opioid consumption,^[5]^ it is not as effective as ISNB^[7]^ and it may not be appropriate to compare it against the gold standard of ISNB. Hence, we decided to compare ESP versus PAI, which is an active treatment but not the present standard.

### Clinical hypothesis

1.1

In patients who undergo arthroscopic shoulder surgery, “ESP block with LA” will provide superior analgesia compared to “PAI with LA.”

### Objectives

1.2

The primary objective of this study is to determine whether ESP block is superior to PAI for in-hospital postoperative analgesia among patients who have undergone arthroscopic shoulder surgical repair. This will be determined by comparing the resting pain scores after initial stabilization in the postanesthetic care unit (PACU).

Secondary objectives will be to compare:

(1)resting pain scores at discharge;(2)pain scores with movement in PACU and at discharge;(3)total opioid consumption in hospital;(4)incidences of postoperative nausea and vomiting (PONV), itching, ipsilateral diaphragmatic paralysis, respiratory depression, and LA toxicity in hospital;(5)sensory blockade assessment in PACU;(6)patient satisfaction at discharge,(7)average pain scores, persistent surgical site pain and opioid use at 24 hours and at 1 month postoperatively.

## Methods

2

### Design

2.1

This will be a single-center RCT with a 2-arm parallel design (Fig. 1) and will be conducted at the St. Joseph's Healthcare Hamilton, affiliated with McMaster University, Canada.

**Figure 1 F1:**
[figure not shown]
ESP versus PAI for arthroscopic shoulder surgeries study consolidated standards for reporting trials flow diagram. ESP = erector spinae plane block, PAI = periarticular infiltration.

### Patient selection

2.2

Eligible patients will be screened during their preanesthetic visit before their surgical date by a trained research assistant using the following selection criteria. Anesthesiologists at the clinic will offer postoperative pain management strategies including the study interventions. Informed consent of willing participants will be obtained along with their baseline parameters. Patients will have the opportunity to withdraw from the study at any point during the surgery or the postoperative phase until their discharge. Baseline parameters will include age, sex, height, weight, body mass index, and the American Society of Anesthesiologists classification.

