#### Primary outcome and measurement

2.5.1

The primary outcome of this study will be to compare the resting pain scores after initial stabilization (30 minutes after admission) in PACU. Pain scores will be noted using the patient-reported numeric rating scale (NRS), an 11-point scale where 0 is no pain and 10 the worst pain imaginable.^[26]^ NRS is validated and considered easy to use.^[27]^

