#### Outcomes at 1 month

2.5.4

Patients will be contacted by telephone at 1 month to ask the following questions:

(1)Are you experiencing any persisting pain at the site of surgery? If yes, please provide details.(2)What is your average daily pain score, on a scale of 0 to 10 (NRS)?(3)Are you continuing to use opioids postoperatively? If yes, provide drug name, frequency and amount over the past 24 hours.(4)How many days per week opioids are used at least once for operative pain?(5)Are you satisfied with your postoperative pain control (Likert scale 1–7)?

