#### Sample size estimation (Table 1)

2.6.1

Existing literature suggests that single-shot ISNBs with general anesthetic could achieve mean postoperative recovery pain scores of 2 to 3 (on a 0–10 visual analog scale),^[35]^ and patients having general anesthetic with PAI block for shoulder surgery report pain scores of 5 to 6 (on a 0–10 NRS) at PACU.^5^,^36^,^37^ We considered a reduction in mean pain scores by 2 points to be clinically meaningful and important. We believe the ESP block has the potential to provide a good quality of analgesia, nearly similar to ISNB with less chance of phrenic nerve blockade. Based on these assumptions, we considered the following for our sample size analysis. For a 2-sided test, assuming a mean pain score of 5.5 (standard deviation of 2.5) in the control (PAI) group, a sample size of 25 per group will have 80% power to detect a statistically significant difference in mean pain scores of 2 or more using a Student *t* test, with an alpha set at 0.05. We expect minimal loss through attrition as the observations happen in hospital before discharge. However, considering the possibility of changes to surgical plan, we decided to set the sample size at 30 per group (which could give us 85% power). Sample size was estimated using (http://biostat.mc.vanderbilt.edu/wiki/Main/PowerSampleSize#PS:_Power_and_Sample_Size_Calculation), version 3.0.43.

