#### Statistical analysis

2.6.2

The trial will be reported as per the consolidated standards of reporting trials standards for reporting randomized trials.^[38]^ The study will be analyzed using an intention-to-treat (ITT) approach. For ITT, we will analyze patients within their randomized groups. We will use multiple imputation strategy to account for missing outcomes in ITT. Normally distributed continuous data will be reported as means and standard deviations; skewed continuous data will be reported as medians and quartiles (Q1 and Q3); and nominal data, categorical or binary data will be reported as counts and percentages. Comparison of normal continuous outcomes will be performed using Student *t* test for unpaired groups. Comparison of non-normal or skewed continuous outcomes will be performed using Mann–Whitney *U* test. Categorical outcomes will be compared using Pearson Chi-squared test. Each test will be 2-sided with a significance level of 0.05. Up-to-date versions of SAS (Cary, NC) and SPSS (Chicago, IL) will be used to conduct all analyses. Dichotomous outcomes will be reported as relative risk and relative risk reductions and continuous outcomes as difference in means with standard deviations. Precision will be reported using 95% confidence intervals. No subgroup tests will be conducted. Individual outcomes and their analyses are summarized in Table 2.

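### No preoperative pain score is listed and the pain outcomes are compared unadjusted: a valid plan, but it forgoes some precision and leaves 1-month persisting pain without a reference point

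*Protocol article*

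**What the plan says.** Section 2.2 (Patient selection) has a trained research assistant screen patients at the preanesthetic visit, where baseline data are taken with consent: "Baseline parameters will include age, sex, height, weight, body mass index, and the American Society of Anesthesiologists classification". No pain score is in this list, and no other part of the article describes a pain measurement before surgery.

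The primary outcome in section 2.5.1 is "resting pain scores after initial stabilization (30 minutes after admission) in PACU", on the 0 to 10 NRS. Section 2.6.2 gives the tests: "Comparison of normal continuous outcomes will be performed using Student *t* test for unpaired groups", and "Comparison of non-normal or skewed continuous outcomes will be performed using Mann–Whitney *U* test". No covariate is mentioned. Section 2.6.1 sizes the trial on the t test.

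Section 1.2 lists persistent surgical site pain at 1 month among the secondary objectives. Section 2.5.4 measures it by telephone: "Are you experiencing any persisting pain at the site of surgery", with details requested if the answer is yes, plus an average daily NRS. Neither item refers to pain before the operation. Section 2.2.2 excludes daily opioid users but not patients with preoperative shoulder pain.

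**The concern.** Patients who come for a shoulder repair may already have shoulder pain. In a trial whose primary outcome is a pain score, preoperative pain on the same scale is the obvious candidate for a prognostic covariate. Leaving it out has three possible consequences.

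- **Precision.** If preoperative pain predicts pain at 30 minutes, an unadjusted comparison leaves explainable variance in the error term.
- **Chance imbalance.** The randomization in section 2.3.1 uses variable blocks and mentions no stratification. With 30 per group, the arms can differ by chance in preoperative pain. Without the measurement, nobody can see or adjust for such a difference.
- **Meaning of a listed outcome.** A yes to the 1-month question may mean unchanged pain, improved pain or new pain after surgery. This point needs no assumed correlation. Preoperative pain cannot be recovered reliably afterwards, so it has to be settled at enrolment.

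**Working it through.** **Inputs from section 2.6.1:** difference 2 NRS points, SD 2.5, 25 per group for 80% power, 30 per group for 85% power; "For a 2-sided test" and "with an alpha set at 0.05". Allocation is 1:1 (section 2.3.1). **Assumed input:** r, the correlation of preoperative NRS with 30-minute resting NRS. The article gives no value, so a range is shown.

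**Step 1. Reproduce the plan's figures.** By the normal approximation, n per group = 2 × (1.960 + 0.842)² × 2.5² / 2² = 24.5, rounded up to 25, which matches. For exact power, use the noncentral t with noncentrality 2 / (2.5 × √(2/n)) and 2n − 2 degrees of freedom:

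- n = 25: noncentrality 2.83, 48 df, power 79.1% (stated 80%).
- n = 30: noncentrality 3.10, 58 df, power 86.1% (stated 85%).

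The unadjusted test therefore has about the power claimed.

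**Step 2. Power with baseline adjustment, 30 per group.** Residual SD = 2.5 × √(1 − r²). Noncentrality = 2 / (residual SD × √(2/30)), with 57 df (one spent on the covariate). The 95% CI half-width is the t quantile × residual SD × √(2/30).

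| Assumed r | Variance removed (r²) | Residual SD | Power | CI half-width (points) |
|---|---|---|---|---|
| unadjusted | 0% | 2.50 | 86.1% | 1.29 |
| 0.1 | 1% | 2.49 | 86.5% | 1.29 |
| 0.2 | 4% | 2.45 | 87.5% | 1.27 |
| 0.3 | 9% | 2.39 | 89.1% | 1.23 |
| 0.4 | 16% | 2.29 | 91.4% | 1.19 |
| 0.5 | 25% | 2.17 | 94.0% | 1.12 |

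**Step 3. Size of a chance imbalance.** The standard error of the standardized baseline difference is √(2/30) = 0.26 SD. A difference beyond 0.25 SD in either direction arises about one time in three, and beyond 0.5 SD about one time in twenty. The resulting shift in the unadjusted estimate is r × 2.5 × imbalance:

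- An imbalance of one standard error (0.26 SD) gives about 0.19 points at r = 0.3 and 0.32 at r = 0.5.
- An imbalance of 0.5 SD gives 0.3 × 2.5 × 0.5 = 0.38 points at r = 0.3 and 0.5 × 2.5 × 0.5 = 0.63 at r = 0.5.

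The target difference is 2 points.

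**Step 4. The 1-month item.** Set section 2.5.4 beside section 2.2: the outcome asks about persisting pain and the baseline list holds nothing for it to persist from. The free-text details may help in single cases but are not a measured reference.

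**The case against.** The strongest reply is that nothing here is wrong. An unpaired t or Mann–Whitney test is valid under 1:1 randomization, its standard error already covers chance imbalance, and the type I error is intact. The stated power reproduces. This stands: a reader might infer that the primary test is invalid or the trial underpowered, and the figures above show otherwise.

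Second, the list is introduced as what the baseline parameters will include, which need not be exhaustive, and Table 2 and the full protocol are not shown. This also stands: the article supports that a preoperative score is not listed, not that it will not be collected.

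Third, r is unknown. A block or infiltration, general anesthesia and individualized IV opioids all come before or around the 30-minute score and could weaken the correlation. That is fair, and at r = 0.1 the gain is negligible.

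Fourth, covariate adjustment is often left to an analysis plan. Here, however, the article itself names the tests, and an analysis plan cannot adjust for a score that was never recorded.

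Fifth, randomization keeps the 1-month comparison between arms unbiased in expectation. True, but it does not define what a yes counts.

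A reader might extend the point to 1-month opioid use. The article does not support that: section 2.2.2 excludes daily opioid use over the past month, and section 2.5.4 asks on how many days per week opioids are taken for operative pain.

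**Conclusion.** The point holds as a cheap improvement to a valid plan. With r between 0.1 and 0.5, the forgone gain at 30 per group runs from 0.4 to about 8 power points, and the CI half-width would fall from 1.29 to between 1.29 and 1.12 points. These sizes rest on the plan's own SD of 2.5 and on an r that the article does not supply. Two consequences do not depend on r: an imbalance in preoperative pain would be invisible, and the 1-month item cannot tell pre-existing from new or persistent post-surgical pain in an individual patient. How far an imbalance would move the primary estimate does depend on r, and it is modest against the 2-point target unless both r and the imbalance are large. All of this applies only if the full protocol does not already record a preoperative score.

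**What to change.** 1. In section 2.2, add a resting and an average shoulder NRS (0 to 10), taken at the preanesthetic visit. If the full protocol already collects them, say so.
2. In section 2.6.2, prespecify the primary analysis as an ANCOVA of the 30-minute resting NRS on arm, adjusted for baseline NRS. Report the adjusted mean difference with its 95% CI whatever the skewness of the scores, so that the primary method does not switch with the distribution. Keep the unadjusted t or Mann–Whitney test as a sensitivity analysis. Adjustment for age and sex is optional.
3. Adjust the 1-month NRS for baseline NRS, and report 1-month persistent pain relative to the preoperative score.

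The cost is one or two questions at an existing visit, a few lines of analysis text and one degree of freedom. If the correlation proves low, little precision is gained, but the 1-month outcome still acquires its reference point.

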#### Inclusion criteria

2.2.1

Patients aged >18 years undergoing elective arthroscopic shoulder joint repairs admitted for a day surgical procedure, with the ability to provide informed consent.

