#### Exclusion criteria

2.2.2

Not consenting; contraindications to spinal injections as per the American Society of Regional Anesthesia and Pain guidelines^[25]^; known allergy to LA; allergy to all opioid medications; diagnostic shoulder arthroscopic procedures; inability to understand or comprehend in English language; history of daily opioid medication use for the past 1 month; and patients with planned overnight hospital stay.

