#### Randomization

2.3.1

Treatment allocation will be done with an allocation ratio of 1:1 using a computer-generated variable block randomization using block sizes of 2, 4, and 6. This randomization list will be prepared by a statistician who is not involved with the study data analysis and provided to the hospital pharmacy. Randomization will happen on the day before surgery. Each patient will be designated a unique randomization code.

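### Any arthroscopic repair is eligible, but the listed baseline data and the test of 30-minute pain leave out the type of repair, so some precision and interpretability may be forgone.

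*Protocol article*

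**What the plan says.** All references are to the protocol article.

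- **Inclusion criteria (2.2.1):** adults "undergoing elective arthroscopic shoulder joint repairs admitted for a day surgical procedure". The type of repair is not restricted.
- **Exclusion criteria (2.2.2):** the only procedure excluded by name is "diagnostic shoulder arthroscopic procedures". Patients with a planned overnight stay are also excluded.
- **Introduction (1):** arthroscopic repairs are "common procedures performed to address different shoulder pathologies".
- **Patient selection (2.2):** "Baseline parameters will include age, sex, height, weight, body mass index, and the American Society of Anesthesiologists classification". No item describes the operation.
- **Randomization (2.3.1):** "computer-generated variable block randomization using block sizes of 2, 4, and 6", at 1:1, on the day before surgery. No stratification factor is stated.
- **Primary outcome (2.5.1):** "resting pain scores after initial stabilization (30 minutes after admission) in PACU", on a 0–10 NRS.
- **Statistical analysis (2.6.2):** "Comparison of normal continuous outcomes will be performed using Student" *t*, and skewed outcomes by Mann–Whitney *U*. Neither comparison has a covariate, and subgroup tests are ruled out.

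**The concern.** The eligible operations are mixed by the plan's own description, and the planned operation has to be known at screening because eligibility depends on it. It is a natural candidate for a baseline variable. It does not appear in the baseline list, in the randomization scheme or in the comparison of the primary outcome.

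If early pain differs by repair type, two things follow. First, the variation between operations stays in the residual of the only powered comparison, where one model term could remove it. Second, with 30 patients per arm the mix of operations will differ somewhat by chance. A reader of the result will want to see by how much, and the listed baseline items would not show it.

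**Working it through.** **1. Inputs from the plan (Sample size estimation, 2.6.1).** Difference 2 points, SD 2.5, two-sided alpha 0.05. The stated power is 80% at 25 per group and 85% at 30 per group.

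**2. Reproducing the plan's figures.** Two-sample *t* test, noncentrality = 2 / (2.5 × √(2/n)).
- n = 25: power 79.1% (exact *t*) or 80.7% (normal approximation), against 80% stated.
- n = 30: power 86.1% (exact *t*) or 87.3% (normal approximation), against 85% stated.

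The stated figures hold.

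**3. Assumptions not in the plan.** Repair type has two levels. A share p of 50%, 70% or 90% has the most common repair. Mean 30-minute pain differs between the levels by d = 1 or 2 NRS points. The SD of 2.5 is the total SD, with case mix already in it.

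**4. Formulas.**
- Share of variance explained: R² = p(1−p)d² / 2.5² = p(1−p)d² / 6.25.
- Adjusted power: residual SD = 2.5 × √(1−R²), with one degree of freedom fewer, at 30 per arm.
- 95% range of the shift from chance imbalance: ±1.96 × d × √(2p(1−p)/30).

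| p | d | R² | Residual SD | Adjusted power | Shift (NRS points) |
|---|---|---|---|---|---|
| 0.5 | 1 | 0.040 | 2.449 | 87.5% | ±0.25 |
| 0.5 | 2 | 0.160 | 2.291 | 91.4% | ±0.51 |
| 0.7 | 1 | 0.034 | 2.458 | 87.3% | ±0.23 |
| 0.7 | 2 | 0.134 | 2.326 | 90.6% | ±0.46 |
| 0.9 | 1 | 0.014 | 2.482 | 86.6% | ±0.15 |
| 0.9 | 2 | 0.058 | 2.427 | 88.1% | ±0.30 |

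If repair type explains nothing (R² = 0), adjusted power is 86.1%, the same as unadjusted. The lost degree of freedom is negligible.

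**5. Is the shift already covered by the standard error?** The unadjusted standard error is 2.5 × √(2/30) = 0.645. In the largest case above, the SD of the imbalance effect is 2 × √(2 × 0.25/30) = 0.258. Its share of the sampling variance is 0.258² / 0.645² = 0.16, which is the R² of that row. The unadjusted confidence interval therefore already allows for it. A simulation of 100,000 trials (30 per arm, two types in equal shares) gave a type I error of 5.0% for d = 1 and 5.1% for d = 2.

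**6. If 2.5 is instead a within-type SD.** Total SD = √(6.25 + p(1−p)d²). With equal shares, d = 1 gives SD 2.550 and power 84.8%, and d = 2 gives SD 2.693 and power 80.8%, both at 30 per arm. The plan does not say which kind of SD it used.

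**7. How often would an imbalance be visible?** For a type with 50% prevalence, the chance that the arms differ by 20 percentage points or more is about 16%. At 30% prevalence it is about 12%.

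**The case against.** The strongest objection is that nothing in the document links repair type to 30-minute pain. The Introduction says only that the pathologies differ. That stands: repair type is a plausible predictor and no more, and every gain above depends on assumed values.

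A reader might infer from the missing covariate that the comparison is biased or its error rate inflated. The documents do not support this, because randomization makes the unadjusted test valid and its standard error covers chance imbalance (step 5). A reader might also infer that the trial is underpowered. That is not supported either. With 2.5 as the total SD the stated 85% is met, and with 2.5 as a within-type SD power stays above 80% for differences up to 2 points.

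The baseline sentence need not be exhaustive, the article condenses a fuller protocol, and its table of outcomes and analyses is not shown. So it cannot be said that an imbalance could never be displayed or adjusted for, only that the items and tests stated here would not do so. For the same reason, the lack of a stratification factor is not an error. Blocked randomization without strata is a legitimate choice for 60 patients.

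Finally, both arms have the infiltration described at the rotator cuff, which is compatible with a mainly cuff population. If so, the gain is at the low end (the p = 0.9 rows). That also stands.

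**Conclusion.** The point holds as a low-cost improvement, and it does not correct an error. Eligibility is broad, the stated baseline items omit the operation, and the stated comparison does not use it. The consequence is forgone precision and a result that is harder to interpret if the arms differ in case mix. The validity of the test and the planned power are intact.

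Under the assumptions in step 3, adjustment is worth roughly 0.5 to 5 percentage points of power (86.1% to between 86.6% and 91.4%). The 95% range for a chance shift in the unadjusted difference is ±0.15 to ±0.51 points, at most about a quarter of the 2-point target. If repair type is weakly prognostic, or nearly all patients have the same repair, there is little or no gain. The power figures refer to the *t* test; the Mann–Whitney alternative was not evaluated.

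**What to change.** 1. Add planned repair type to the baseline form, in two levels (for example rotator cuff repair versus other), recorded before randomization. Use the planned operation and not the one performed, so that the covariate is fixed before allocation. The sample size section itself expects some changes to the surgical plan.
2. Tabulate planned repair type by arm.
3. Prespecify a linear model of the 30-minute NRS with arm and planned repair type as the primary analysis, and report the adjusted mean difference with its 95% CI. This is a main-effect covariate and does not conflict with the rule against subgroup tests.
4. Optionally, stratify the randomization list on the same factor, but only if the list is not yet in use.

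The cost is one form field and one degree of freedom, with no added patients or procedures. If the full protocol already records the operation, only steps 2 and 3 remain.
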